### Sample size

The sample size was estimated to detect a non-negligible and useful effect size in the primary outcome, TEMPA, corresponding to Cohen’s d =  0.4 (f =  0.2), when applying ANOVA with a significant interaction effect (time*intervention) [30]. Considering two assessments, five groups, a significance level of 0.05 with 80% power, and accounting for an additional 19% margin for attrition, a total of 95 participants will be required, distributed into 19 participants per group.

Recruitment will be based on dissemination through electronic, radio, and print media, as well as contact with municipal health departments and associations as a strategy to achieve the target sample size.

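### The sample size equates Cohen's d = 0.4 with an interaction f = 0.2; in this five-arm, two-time design that f means a best-versus-worst difference in TEMPA change of about 0.8 to 1.3 SD

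*Protocol article*

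**What the plan says.** The Sample size section of the protocol article states: "The sample size was estimated to detect a non-negligible and useful effect size in the primary outcome, TEMPA, corresponding to Cohen’s d" of 0.4, with f = 0.2 in brackets as its equivalent. The powered test is the interaction: "when applying ANOVA with a significant interaction effect (time*intervention"). The remaining inputs are "Considering two assessments, five groups", "a significance level of 0.05 with 80% power", and the final step is "accounting for an additional 19% margin for attrition, a total of 95 participants will be required, distributed into 19 participants per group".

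The section does not give the T0–T1 correlation of TEMPA, the SD to which d refers, or the pattern of arm means that f = 0.2 stands for.

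Under Randomization, allocation and blinding, all five groups receive an active intervention. Under Statistical analysis, the group-by-time interaction is assessed by mixed ANOVA or GEE, with Sidak's test for multiple comparisons.

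**The concern.** Cohen's d is by convention a standardised difference between two means. A reader of the Sample size section will therefore take the target to be a 0.4 SD difference between interventions, detectable with 80% power. The f that drives the calculation is a different quantity: it measures the spread of interaction effects over five arms and two times. The rule d = 2f links the two only when there are two equal groups and one contrast.

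Because every arm is active, the interaction carries the randomised comparison between the approaches. If the stated detectable effect is two to three times too small, the article misdescribes how sensitive the trial is on its primary question.

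**Working it through.** **Inputs from the Sample size section.** f = 0.2, d = 0.4, k = 5 groups, m = 2 assessments, alpha 0.05, power 80%, 19% margin, N = 95. The T0–T1 correlation rho is not given and is treated as unknown.

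**Step 1: reproduce 95.** For a within-between interaction in a mixed ANOVA, the noncentral F has df1 = (k − 1)(m − 1) = 4, df2 = (N − k)(m − 1) = N − 5 and λ = f²·N·m/(1 − rho).

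With rho = 0.5 and N = 80, λ = 0.04 × 80 × 2/0.5 = 12.8 and power is 80.3%. At N = 75, the next smaller balanced total, power is 77.1%. Then 80 × 1.19 = 95.2, which gives 95, or 19 per group.

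At f = 0.2, other correlations do not lead to 95:

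| rho | evaluable N | × 1.19 |
|---|---|---|
| 0.3 | 110 | 130.9 |
| 0.5 | 80 | 95.2 |
| 0.6 | 65 | 77.4 |
| 0.7 | 50 | 59.5 |
| 0.8 | 35 | 41.7 |

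Values slightly above 0.5 (0.51 and 0.53 were tried) also give a balanced total of 80. The implied planning value is therefore about 0.5.

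**Step 2: what f = 0.2 means here.** With two times, each arm's interaction effect in a cell is plus or minus half the deviation of its mean change from the average change. Hence f = SD(arm mean changes)/(2σ), where σ is the SD at a single time. So f = 0.2 means SD(arm mean changes) = 0.4σ.

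Let D be the largest between-arm difference in change. Then Var(arm mean changes) = c·D², where c depends on the pattern of the five arms, and D = 0.4σ/√c:

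| Pattern of the five arms | c | D at f = 0.2 |
|---|---|---|
| Two arms against three | 0.24 | 0.82 SD |
| One arm differs | 0.16 | 1.00 SD |
| Evenly spaced | 0.125 | 1.13 SD |
| One high, one low, three midway | 0.10 | 1.26 SD |

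The figure of 0.4 is the spread across arms, not the difference between any two of them.

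**Step 3: power if D = 0.4 SD.** Now λ = N·c·D²/[2(1 − rho)]. With N = 80 and rho = 0.5, λ = 80 × 0.16 × c = 12.8c, which runs from 1.28 to 3.07. Interaction power with 80 evaluable:

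| Pattern | rho 0.3 | rho 0.5 | rho 0.7 | rho 0.8 | rho 0.9 |
|---|---|---|---|---|---|
| One high, one low | 9.7% | 11.8% | 17.2% | 24.5% | 47.1% |
| Evenly spaced | 11.0% | 13.8% | 20.8% | 30.2% | 57.4% |
| One arm differs | 12.9% | 16.6% | 26.0% | 38.2% | 69.7% |
| Two against three | 17.6% | 23.6% | 38.2% | 55.4% | 87.7% |

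If all 95 are evaluable, the range at rho = 0.5 is 13.4 to 27.9%.

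If d is instead counted in SDs of the change score, the factor 2(1 − rho) cancels, λ is again 12.8c, and power is 12 to 24% whatever the correlation.

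**Step 4: one pairwise contrast of 0.4 SD at rho = 0.5.** With 16 per group, power is 20% unadjusted and 4.5% after Sidak for 10 contrasts (alpha 0.00512). With 19 per group it is 23% and 5.6%.

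**The case against.** **The sample size is correct for its f.** This stands. The article prints f = 0.2 beside d, names the test, and arrives at the right total. A reader might infer that 95 is a miscalculation or that more participants are needed; the documents do not support that. What is wrong is the translation of f into d.

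**The article never says d is a best-versus-worst difference, and 0.4 is a real quantity in this design.** It is the SD of the arms' mean changes in units of σ. That is not what d denotes, though, and nothing in the section redefines it. A reader will take the ordinary meaning, and for that meaning the power claim fails.

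**The power figures rest on an unstated correlation.** This stands as a condition. A correlation of about 0.5 is inferred from the article's own numbers as the planning value; the true TEMPA correlation is not in the documents. At 0.9, the most favourable pattern would exceed 80% power for a 0.4 SD difference. The planned 80 evaluable cannot come from that value, since f = 0.2 would then need only about 25. A more generous convention, entering the spread of the arms' changes as f without halving it (f = 0.126 to 0.196), still gives only 38 to 79% at correlation 0.5.

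**The attrition step.** A reader might infer an error because 80/0.81 = 98.8 rather than 95. The article describes an added margin, and 15 added to 80 is 18.75%, or 19% rounded. It does not state a 19% dropout rate, so there is no contradiction.

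**The harm is speculative.** Partly so. The article does not plan to conclude equivalence from a null interaction. It reports means with 95% confidence intervals, and its Discussion asks for larger trials. The misstatement concerns the trial's stated sensitivity, not a planned inference.

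**Conclusion.** The point holds as a misstated detectable effect. The design has 80% power, with 80 evaluable and a correlation of about 0.5, for an interaction f = 0.2, which is a largest between-arm difference in TEMPA change of about 0.8 to 1.3 single-time SDs. That is two to three times the 0.4 that the article names. For a largest difference of 0.4 SD, power with 80 evaluable is about 12 to 24% at correlation 0.5, and between about 10% and 88% over correlations of 0.3 to 0.9 and the four patterns of arms.

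These figures assume equal group sizes, the omnibus interaction test at 0.05, and an effect scaled by the single-time SD. The result does not show that N = 95 is wrong or that the margin was misapplied, and the 12 to 24% should not be quoted without its correlation. The point should be corrected, but it does not threaten the conduct of the trial.

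**What to change.** Keep N = 95 and amend the Sample size section:

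- Delete Cohen's d = 0.4.
- State the T0–T1 correlation that was assumed (the numbers imply about 0.5).
- Restate the target: 80 evaluable participants give 80% power for an interaction f = 0.2, meaning an SD of 0.4 across the arms' mean changes and a best-versus-worst difference in TEMPA change of about 0.8 to 1.3 SD, depending on the pattern of arms.
- Add the power for a 0.4 SD between-arm difference as conditional on the correlation: 12 to 24% at 0.5, 17 to 38% at 0.7, 25 to 55% at 0.8.

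The margin needs no correction. If useful, note that 95 enrolled leaves 80 evaluable with up to 15.8% loss (15/95).

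The cost is a wording amendment. Design, analysis and number of participants stay the same; the stated detectable effect becomes less favourable.

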### Statistical analysis

The results of qualitative variables will be expressed as absolute and relative frequency. Symmetric quantitative variables will be presented as mean and standard deviation, and asymmetric ones as median and interquartile range [P25 - P75]. The normality of the data will be checked using the Shapiro-Wilk test. Group characteristics will be compared using the Chi-square test, ANOVA, and/or false discovery rate (FDR) for the multiple comparisons between the 5 groups.

a) A mixed repeated-measures ANOVA will be used, or, in the absence of normality and/or in the presence of missing data, generalized estimating equations (GEE) models will be applied to assess the main effects of group and time, and the group*time interaction, with an unstructured correlation matrix. The goodness of fit will be assessed using the Quasi-Likelihood under Independence Model Criterion (QIC). The best-fitting distribution for the data (normal or gamma) will be evaluated using the AIC criterion, with identity or logarithmic link functions, respectively. Sidak’s test will be used for multiple comparisons. The results will be presented as means and 95% confidence intervals (CI). Analyses will be conducted using SPSS software (IBM SPSS Statistics for Windows, Version 25.0. Armonk, NY: IBM Corp.). The significance level will be set at 0.05.

### 
Trial status

Participant recruitment began in February 2023. Data collection and data analysis are expected end by September 2026.

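### Any missing value moves the primary TEMPA test from the ANOVA F test used for sizing to a GEE that is anti-conservative at about 15 per arm, with the effect scale chosen by AIC

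*Protocol article*

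**What the plan says.** The Sample size section bases the trial on the time-by-intervention interaction in an ANOVA of TEMPA, with f = 0.2. It uses these inputs: "Considering two assessments, five groups", "a significance level of 0.05 with 80% power", and "accounting for an additional 19% margin for attrition". The result is "a total of 95 participants will be required, distributed into 19 participants per group".

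The Statistical analysis section names a mixed repeated-measures ANOVA first, and then adds that "in the absence of normality and/or in the presence of missing data, generalized estimating equations (GEE) models will be applied", "with an unstructured correlation matrix". QIC is named for goodness of fit. A separate step follows: "The best-fitting distribution for the data (normal or gamma) will be evaluated using the AIC criterion, with identity or logarithmic link functions, respectively". Sidak's test is used for the multiple comparisons, and results are to be given as means with 95% confidence intervals.

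The article does not state whether the GEE covariance is robust or model-based, which test statistic is used, whether a small-sample correction applies, or which fit supplies the AIC.

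**The concern.** The fallback is written as an exception, but its trigger is a single missing value and the plan itself expects losses. The analysis that will be run is then not the one that set the sample size.

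Two things are at stake. First, the usual GEE tests rely on many participants per arm. Here there are about 15 to 16 with both assessments, so a nominal 5% test of the primary outcome may not be a 5% test. Second, the model for the primary outcome is settled by a fit statistic computed on the trial data. That statistic does not belong to GEE, and the choice carries the link function with it. The reported treatment effect could thus be a difference between arms in change or a ratio of changes, depending on the data.

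**Working it through.** **1. The plan's own figure.** Inputs from the Sample size section: f = 0.2, k = 5 groups, m = 2 assessments, alpha 0.05, power 0.80. The correlation between assessments is not stated; I assume rho = 0.5.

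Noncentrality = f² × N × m / (1 − rho), on (k − 1)(m − 1) = 4 and N − 5 degrees of freedom.

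With N = 80: 0.04 × 80 × 2 / 0.5 = 12.8 on 4 and 75 df, power 0.803. Adding 19%: 80 × 1.19 = 95.2, taken as 95, or 19 per arm. The stated size is reproduced, and it is the size for an F test.

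**2. Participants with both assessments.** At 19% loss: 95 × 0.81 = 76.95, about 15.4 per arm. If exactly 80 complete: 16 per arm.

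**3. Chance that the switch is not triggered by missing data.** P(no missing T1 value among 95) = (1 − loss rate)^95.
- 19% loss: 0.81^95 = 2 × 10⁻⁹
- 5% loss: 0.95^95 = 0.8%
- 2% loss: 0.98^95 = 15%

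A failed normality check triggers the switch as well.

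**4. Type I error of the 4-df interaction test, nominal 0.05.** Simulation under the null: five arms, two assessments, 19 randomised and 15 completers per arm, loss at T1 completely at random. Assumptions not in the article: rho = 0.5; normal data with a coefficient of variation of about 0.25, or gamma data with shape 2. There were 10,000 replicates (Monte Carlo error about 0.3 percentage points), or 4,000 for the rows marked * (up to about 0.5 points).

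| Test | Normal data | Gamma data |
|---|---|---|
| GEE, identity link, robust Wald chi-square | 0.1005 | 0.0904 |
| GEE, log link, robust Wald chi-square | 0.0985 | 0.1256 |
| GEE, identity link, model-based variance* | 0.0848 | 0.0630 |
| GEE, log link, model-based variance* | 0.0912 | 0.1035 |
| GEE, robust with AIC choice of model* | 0.1050 | 0.1258 |
| GEE, identity, statistic × 14/15, referred to F(4, 42) | 0.0614 | 0.0571 |
| ANOVA of change (the mixed-ANOVA interaction), F test | 0.0460 | 0.0499 |
| ANCOVA of T1 on baseline, F test | 0.0458 | 0.0491 |

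For the AIC row, AIC was taken from an independence GLM.

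With 16 completers of 19, the robust test gives 0.088–0.090 (identity) and 0.087–0.118 (log). With no loss it gives 0.085–0.090 and 0.086–0.110. With 80 completers of 100 per arm it falls to 0.054–0.064, so this is a small-sample effect. Part of it is the missing denominator df alone: using the chi-square critical value where F(4, 70) applies gives 0.061. The Sidak pairwise familywise error with robust tests under the identity link is 0.074–0.083 at 15 completers.

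Two further simulations with 19 randomised per arm and 19% of T1 missing agree. One gave 9.5% (robust), 7.7% (model-based) and 6.5% (bias-reduced). The other, with rho = 0.5, gave 10.0% (robust), 6.4% (model-based with chi-square) and 5.2% for a REML linear model with an F reference.

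**5. AIC and the link.** AIC needs a likelihood. GEE is defined by estimating equations and has none, so the AIC must come from some other fit, such as a GLM that treats the two assessments as independent.

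Under identity, the interaction is the between-arm difference in (T1 − T0). Under log, it is the ratio of T1/T0 between arms. Take one arm going from 60 to 48 and another from 72 to 60. The differences are −12 and −12, so the additive interaction is 0. The ratios are 48/60 = 0.80 and 60/72 = 0.83, so the ratio interaction is not null. With equal baselines, for example 60 to 55 in both arms, both contrasts are zero.

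**The case against.** The strongest reply is that the article does not name a robust covariance or a Wald chi-square test. Those details may properly sit in an analysis plan that is not shown. This stands. A reader might infer that the plan doubles its type I error whatever is done, and the documents do not support that: the figure of about 10% belongs to the uncorrected robust test. Model-based variance gives about 6–10%, and a variance correction with an F reference about 6%. What remains is that the article sends the test to GEE without any correction, and every GEE variant tried at 15 completers per arm was above 5%.

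A reader might also infer that the AIC step cannot be carried out. It can, if AIC is borrowed from an independence GLM. The step is poorly specified, not impossible, and QIC is named for a different purpose.

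A third tempting reading is that the log link changes the null hypothesis. Under randomisation the arms have equal expected baseline means, and then the two nulls coincide. The 60 versus 72 example needs a chance baseline difference. What the link does change is the effect measure.

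Finally, it may look as if the analyst could pick the scale after seeing results. The rule is mechanical, each link is tied to a distribution, and the Randomization, allocation and blinding section promises blinded analysis. Selection by itself also adds little error: 0.105 on normal data against about 0.10 for either fixed link, and on gamma data the same as the fixed log link. The objection to the AIC step is therefore a data-dependent effect measure and an undefined criterion, not discretionary choice.

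**Conclusion.** The point holds in this form. The switching rule is stated in the article, so it is not a detail left to another document. At the planned attrition it will almost surely make GEE the primary analysis of TEMPA, in place of the F test used for sizing. With about 15 to 16 completers per arm and no correction stated, the interaction test runs at about 9–10% (robust, identity), about 10–13% (robust, log, 15 completers) or about 6–10% (model-based), against about 5% for an F-referenced linear analysis. These figures assume rho = 0.5, loss completely at random and the outcome shapes given above. The excess varies with the estimator and the link. The AIC step is not defined for the GEE fit and leaves the effect measure to the data, although the null is unchanged when baseline means are equal.

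**What to change.** Prespecify one primary model for TEMPA: a normal, identity-link linear mixed model for T0 and T1, fitted by REML to all available data, with the group-by-time interaction tested by an F test with Satterthwaite degrees of freedom (SPSS MIXED). For this outcome, remove the switch on normality or missing data and the AIC choice of distribution and link. If GEE is kept, make it a sensitivity analysis with a named small-sample-corrected variance.

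The cost is a change of wording. The same software serves, and no extra participants or visits are needed. The Protocol amendments section provides the route. Under Trial status, data collection and analysis are expected to end by September 2026, so the change should be filed before anyone sees results by group.

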**Fig 2 pone.0315148.g002:**
[figure not shown]
Flowchart of participant distribution throughout each stage of the study. AO, action observation; BMI, brain machine interface; AE, action execution; EG, experimental group; MI, motor imagery.

Allocation will be carried out by a blinded investigator who will not be involved in the intervention. The randomization process will be carried out with a 1:1 allocation ratio through the website randomizer.com. It will not be possible to blind the participants and researchers who will carry out the training. However, the study will be blinded to the researchers for results and statistical analysis. This is a single-blind study, as the therapists (physical and occupational therapists) conducting the interventions will be different from those responsible for administering the assessment tools during data collection phases. Additionally, the blinding of data analysis will be ensured.

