### Outcome

As the main outcome of the study, an improvement in the TEMPA score is expected, along with a decrease in the execution speed of tasks, indicating that participants experienced positive impacts on upper limb motor symptoms after interventions involving action observation, motor imagery, and brain-machine interface. As for secondary outcomes, improvements in motor symptoms are anticipated, evidenced by lower scores on the UPDRS-III and reduced time in the 9 Hole-Peg Test, as well as enhancements in cognitive symptoms indicated by increased scores on the PD-CRS. Additionally, it is expected that the interventions will also have a positive effect on occupational performance, leading to better performance and satisfaction in daily activities as assessed by the COPM. The averages of the assessments will be considered, with measurements for each outcome taken at T0 and T1, and at T2 regarding perceptions of changes in motor and cognitive conditions, as well as the COPM.

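### The primary TEMPA test compares change scores; using the T0 score as a covariate would be more efficient, with a gain that depends on an unstated T0–T1 correlation

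*Protocol article*

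**What the plan says.** The Statistical analysis section of the protocol article names a mixed repeated-measures ANOVA. If normality fails or data are missing, it names GEE with an unstructured correlation matrix and either a normal distribution with identity link or a gamma distribution with log link. The purpose is "to assess the main effects of group and time, and the group*time interaction". No baseline covariate is named, and nothing constrains the groups to a common T0 mean.

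The Outcome section describes the schedule, "with measurements for each outcome taken at T0 and T1". T2 is reserved for the COPM and the perceived-severity questions, as the Data collection section confirms. TEMPA therefore has exactly two occasions.

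The Sample size section powers the time-by-intervention interaction on TEMPA at d = 0.4 (f = 0.2): "Considering two assessments, five groups, a significance level of 0.05 with 80% power". After "accounting for an additional 19% margin for attrition", it concludes that "a total of 95 participants will be required, distributed into 19 participants per group".

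**The concern.** T0 TEMPA enters the model as one of two outcome occasions. With two occasions, the group-by-time interaction asks only whether mean change differs between groups. In a randomised trial the groups share the same expected T0 mean, so the T0 score can instead serve as a covariate. Subtracting the whole T0 score fixes its coefficient at 1. ANCOVA estimates the coefficient (ρ, when the variances are equal), which removes more noise and does not over-correct a chance imbalance at T0.

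At stake is precision in a five-group trial with 19 per group before attrition. The same applies to the other outcomes measured at T0 and T1, and to the Sidak-adjusted pairwise comparisons. The sample-size calculation addresses only the overall interaction test, not those comparisons.

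**Working it through.** **Inputs from the article.** k = 5 groups, m = 2 assessments, f = 0.2, α = 0.05, power 80%, attrition margin 19%, total 95, equal allocation.

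**Input not stated.** The T0–T1 correlation ρ. It is inferred below and then varied.

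**Step 1: reproduce the stated sample size.** For the within-between interaction, the noncentrality is λ = f²·N·m/(1−ρ), with (k−1)(m−1) = 4 and (N−k)(m−1) = N−5 degrees of freedom. At ρ = 0.5:

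- N = 79: λ = 0.04 × 79 × 2/0.5 = 12.64, power 79.7%
- N = 80: λ = 0.04 × 80 × 2/0.5 = 12.80, power 80.3%

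So 80 evaluable participants are needed, and 80 × 1.19 = 95.2, which is the stated 95 = 5 × 19. Other correlations do not return 95: the number before attrition is 110 at ρ = 0.3, 95 at 0.4, 65 at 0.6 and 50 at 0.7. Dividing by 0.81 instead of multiplying by 1.19 gives 99.

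**Step 2: identify the test.** With two complete occasions, the interaction F test is the one-way ANOVA of D = T1−T0. The identity-link GEE contrast on complete data is likewise the difference in mean change.

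**Step 3: compare residual variances.** With a common variance of 1 at T0 and T1:

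- change score: 2(1−ρ)
- ANCOVA: 1−ρ²
- ratio: (1−ρ²)/[2(1−ρ)] = (1+ρ)/2

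The ratio is 0.65 at ρ = 0.3, 0.75 at 0.5, 0.85 at 0.7 and 0.90 at 0.8.

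**Step 4: compute power.** Under this convention the variance of the group effects on change is 4f² = 0.16. Hence λ(change) = 0.16N/[2(1−ρ)] with 4 and N−5 df, and λ(ANCOVA) = 0.16N/(1−ρ²) with 4 and N−6 df.

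| Evaluable N | ρ | λ change | Power, change | λ ANCOVA | Power, ANCOVA |
|---|---|---|---|---|---|
| 80 | 0.5 | 12.80 | 80.3% | 17.07 | 91.2% |
| 77 | 0.5 | 12.32 | 78.5% | 16.43 | 89.9% |
| 80 | 0.3 | 9.14 | 64.0% | 14.07 | 84.3% |
| 80 | 0.7 | 21.33 | 96.4% | 25.10 | 98.5% |
| 80 | 0.8 | 32.00 | 99.7% | 35.56 | 99.9% |

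The row with 77 is what remains if 19% of 95 are lost (95 × 0.81 = 76.95). A simulation of 20,000 trials with 16 per group at ρ = 0.5 gave 80.8% and 91.1%, in agreement with the first row.

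**The case against.** The strongest reply is that this is a preference for efficiency and not an error. Under randomisation the interaction test is unbiased and keeps its type I error. It is also the test on which the sample size rests, and it reaches its 80% target under the inferred inputs. That stands. A reader might infer that the planned analysis is invalid, or that the interaction test is itself a test of T0 group means. Neither follows: the interaction contrasts mean change. A reader might also infer that the T0 data go unused, but T0 is in the model as an outcome occasion.

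Second, the figure of 91% depends on ρ = 0.5, which the article does not state. TEMPA is repeated about two weeks apart, so a higher correlation is plausible, and at 0.7 or above the gain with 80 evaluable is about two points or less. That also stands, and is why the range is shown.

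Third, the meaning of f is inferred. If f = 0.2 described the spread of the group differences themselves (variance 0.04), power with 80 evaluable at ρ = 0.5 would be about 24% for change and 32% for ANCOVA. That convention would not lead to 95 participants; the one used here does.

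Fourth, the change-score identity does not cover every branch. It is not exact for the gamma/log-link GEE or for incomplete pairs under GEE, and some attrition is expected.

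Fifth, covariates are often left to an analysis plan that is not shown. Here, however, the article itself lists the model terms, so the choice is fixed in the text.

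**Conclusion.** The point holds as a matter of efficiency. For the ANOVA, and for the identity-link GEE with complete data, the planned primary test is a change-score test. Adjusting for the T0 score already collected cuts residual variance by the factor (1+ρ)/2, assuming equal variances at T0 and T1.

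Under ρ = 0.5 and the definition of f that reproduces 95, the gain is about 11 percentage points of power, with either 80 or 77 evaluable. It is about 20 points at ρ = 0.3, 2 at ρ = 0.7 and a fraction of a point at ρ = 0.8, with f and N held fixed. It would be wrong to read the 11 points as a property of the trial independent of ρ. The direction does not depend on ρ: the variance ratio is below 1 for every ρ below 1, and the price is one residual degree of freedom. The change is worth making, but the trial's validity does not hang on it.

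**What to change.** Before analysis, amend the Statistical analysis section so that the primary analysis is T1 TEMPA on group with T0 TEMPA as covariate (ANCOVA). A repeated-measures model with T0 means constrained equal across groups would also serve. Treat the other outcomes measured at T0 and T1 in the same way. Annotate the Sample size section to say that 95 was derived for the unadjusted interaction, and state the correlation assumed.

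The Interventions section has GE4 and GE5 try their intervention on the T0 day without giving the order. Confirm that the T0 measures are taken before that familiarisation. Otherwise T0 is not a pre-exposure score in those two groups, and neither covariate adjustment nor an equal-means constraint would be safe.

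The cost is one residual degree of freedom and a formal amendment by the route in the Protocol amendments section. Recruitment began in February 2023, so this changes the primary analysis of a running trial and should be dated and completed before any comparison by group. No new data, visits or participants are needed.
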